## Abstract

**Background:**

An in-depth epidemiological investigation on intestinal parasite infections in an impoverished area of Port Elizabeth, South Africa provides a unique opportunity for research on its impact on children’s physical fitness, cognitive performance and psychosocial health. Additionally, we will screen risk factors for the development of diabetes and hypertension in adulthood.

**Methods/Design:**

A 2-year longitudinal cohort study will be conducted, consisting of three cross-sectional surveys (baseline and two follow-ups), in eight historically black and coloured (mixed race) primary schools located in different townships in Port Elizabeth, South Africa. Approximately 1000 Grade 4 primary schoolchildren, aged 8 to 12 years, will be enrolled and followed. At each survey, disease status, anthropometry and levels of physical fitness, cognitive performance and psychosocial health will be assessed. After each survey, individuals diagnosed with parasitic worm infections will be treated with anthelminthic drugs, while children with other infections will be referred to local clinics. Based on baseline results, interventions will be tailored to the local settings, embedded within the study and implemented in half of the schools, while the remaining schools will serve as controls. Implementation of the interventions will take place over two 8-week periods. The effect of interventions will be determined with predefined health parameters.

**Discussion:**

This study will shed new light on the health burden incurred by children in deprived urban settings of South Africa and provide guidance for specific health interventions. Challenges foreseen in the conduct of this study include: (i) difficulty in obtaining written informed consent from parents/guardians; (ii) administration of questionnaires in schools where three languages are spoken (Afrikaans, Xhosa and English); (iii) challenges in grasping concepts of psychosocial health among schoolchildren using a questionnaire; and (iv) loss to follow-up due to the study setting where illiteracy, mobility and violence are common. Finally, designing the health interventions together with local principals and teachers will allow all concerned with the research to bolster a sense of community ownership and sustained use of the interventions after the study has ceased.

**Trial registration:**

Controlled-trials.com; identifier: ISRCTN68411960 (date assigned: 14 February 2014).

## Background

As traditional lifestyle and diet change alongside socioeconomic developments, countries are starting to experience a double burden of communicable and non-communicable diseases in the face of weak health systems [1, 2]. Many countries still struggle to meet the existing challenges stemming from infectious diseases, such as malaria and intestinal parasite infections. Meanwhile, non-communicable diseases, such as diabetes, cardiovascular diseases, obesity-related conditions and cancers, impose a growing burden on them [3]. This phenomenon has been recognised by the global health community and must be addressed in the new era of the sustainable development goals (SDGs), particularly “to ensure healthy lives and promote well-being for all at all ages” [4], while the unfinished agenda of the communicable diseases during the millennium development goal (MDG) era must be accelerated.

In South Africa, investigations of physical activity patterns of primary schoolchildren attending schools in disadvantaged neighbourhoods have confirmed that physical activity levels are insufficient [5]. These school environments are usually not conducive for the promotion of physical activity due to inadequate sport and recreation facilities, a lack of qualified teachers and an irregular physical education program. In 2010, Kimani-Murage *et al.* [6] reported that in a low-income South African setting, the co-prevalence of early stunting and adolescent obesity in girls is a result of increasing levels of physical inactivity. This observation was particularly prevalent among black girls, who were found to have the highest rates of physical inactivity [7]. As physical inactivity during childhood can lead to poor health outcomes in adulthood [8], there is a pressing need to promote physical activity among school-aged children in disadvantaged communities in order to prevent obesity-related conditions and other non-communicable diseases. Additionally, infectious diseases that are intimately connected with poverty may also occur in disadvantaged South African schools [9]. These infections can have a negative impact on children’s nutritional status, cognitive abilities and physical fitness [10, 11]. Such a dual burden of disease can put children at a high risk of compromised health, poor subjective well-being, hampering their growth and economic perspectives.

In particular, it is hypothesized that, first, intestinal parasite infections have a negative influence on the physical fitness, cognitive performance, nutritional status and psychosocial health of school-aged children in deprived urban South Africa. Second, the development of setting-specific health interventions can decrease the incidence of parasitic infections and insulin resistance as well as elevated blood pressure, and thereby the risk of developing non-communicable conditions later in life, such as diabetes and hypertension (Fig. 1). An in-depth epidemiological study on intestinal parasite infections in an impoverished part of Port Elizabeth, South Africa, will provide a unique opportunity for research on its impact on children’s physical fitness, cognitive performance and psychosocial health. In addition, a search for risk factors for the development of diabetes and hypertension in adulthood seems justified. From this research, an evidence-base will be created to design setting-specific health interventions. The purpose of this article is to present the detailed protocol of the proposed study.

**Fig. 1 Fig1:**
[figure not shown]
A conceptual framework for the DASH study

### Goal and objectives

The goal of this project is to survey the distribution of selected intestinal parasite infections and risk factors for non-communicable conditions, and assess their impact on schoolchildren’s health over time in the face of tailored interventions in eight townships of Port Elizabeth, South Africa before, during and after the introduction of setting-specific interventions. We will pursue two specific objectives:(i)to conduct a longitudinal study assessing the prevalence of intestinal parasites, risk factors for diabetes and hypertension, anthropometry and the level of physical fitness, cognitive performance and psychosocial health among schoolchildren; and(ii)to design setting-specific interventions and assess their effect on the measured health parameters.

## Methods/Design

### Study area

The study will be conducted in historically black and coloured (mixed race) government primary schools from various areas in Port Elizabeth in the south-east part of South Africa (Fig. 2). The areas populated by black Africans are commonly referred to as townships and include the areas of Kwazakhele, New Brighton, Zwide, and Motherwell. The “Northern areas” in Port Elizabeth are largely made up of coloured people who were forcefully relocated from the central areas of the city to the outlying northern areas, and include the areas of Schauderville, Gelvandale, Helenvale, Hillcrest and Booysens Park [12, 13]. Government schools in South Africa are classified into 5 groups, called quintiles, mainly for the purpose of allocating financial resources, with quintile 1 being the poorest and quintile 5 being the “least poor”. Schools in quintiles 1, 2 and 3 are proclaimed as no-fee schools, while schools in quintiles 4 and 5 are fee-paying schools [14]. The eight schools who will be participating in the DASH study belong to quintiles 3. Furthermore, the study area has been detrimentally affected by extreme poverty and high rates of unemployment, due to past government policies, as well as current public health and economic challenges faced by the country [7].

**Fig. 2 Fig2:**
[figure not shown]
Study area and location of schools participating in the DASH study

### Study design

The study duration spans from February, 2015 to June, 2017 (Fig. 3). The longitudinal cohort study consists of three cross-sectional surveys (baseline, mid- and final follow-up). At each survey time point, disease status, anthropometry and levels of physical fitness, cognitive performance and psychosocial health are measured. After each survey, infected individuals are either treated with anthelminthics (400 mg albendazole, single dose) for soil-transmitted helminths [15] and/or referred to local clinics for the management of other intestinal parasite infections. Based on results from the baseline survey, a package of setting-specific interventions is designed together with local students, teachers, school volunteers and parents. The intervention package consists of three main components:

**Fig. 3 Fig3:**
[figure not shown]
A pictorial display of the design and timeline of the DASH study

(i)Physical activity [9, 16]: Regular physical activity opportunities, including two physical education (PE) lessons a week, weekly dancing-to-music classes, and in-class activity breaks will be incorporated into the main school curriculum and a physical activity friendly school environment will be created. These approaches could help improve children’s physical fitness, and positively affect their psychosocial health [17–21].(ii)Health education [22]: A series of classroom-based lessons will be developed to help increase the awareness for intestinal parasite infections among the schoolchildren and educate them on treatment and prevention methods, such as proper hygiene, sanitation habits and the importance of consuming clean water and food. It is also planned that schoolchildren will produce a theatre play to convey key messages they have learnt through the health education.(iii) Nutritional interventions: A series of classroom-based lessons will be developed to help increase the awareness of the importance of healthy nutrition. In addition, an analysis of the school feeding programme will be done to identify ways to improve their current diet to be healthier. The schoolchildren will also be given a ready to use supplementary food (RUSF) in the form of an enriched lipid-based paste. The cooks in the schools will also be trained in basic nutrition and hygiene during preparation of the school meals.

The interventions will be embedded within the longitudinal study and be implemented in half of the schools, while the remaining schools will serve as controls. The intervention schools were either selected due to the soil-transmitted helminth prevalence, number of Grade 4 learners, geographical location and affiliation to a particular ethnic group or commitment of teachers or school staff. Implementation of the interventions will take place twice; in July-September, 2015, after the baseline survey, and in February-March, 2016, after the first follow-up. The first follow-up will allow the implementation feasibility of the designed interventions to be determined through focus-group discussions with teachers and students, while the subsequent surveys will allow assessing their impact on the measured health parameters.

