### Data analysis

The primary objectives of the statistical analysis will be to assess (i) the prevalences of infections and conditions, and their associations with physical fitness, nutritional status, cognitive performance and psychosocial health at baseline and over time; and (ii) the effects of interventions on disease status and other health parameters. The secondary objective will be to assess the feasibility and acceptability of the health interventions implemented.

Parasitological status will be assessed in terms of prevalence and intensity of infection with specific parasite species and the extent of multiparasitism. Clinical and anthropometric indicators, physical fitness, cognitive performance and psychosocial health scores will be characterised by their mean and standard deviation if they are normally distributed and by their median and interquartile range otherwise. Questionnaire data pertaining to the psychosocial health will be expressed as percentages. All indicators will be compared between physically fit/non-infected and physically unfit/infected children and between intervention and control schools.

To assess the effects of the different interventions on the parasitological status, clinical and anthropometric indicators, physical fitness, cognitive performance and psychosocial health, the following statistical procedures will be employed:(i)Mixed logistic regression models with random intercepts for schools will be used to compare binary data, such as parasitological status and clinical indicators, between the intervention and control groups.(ii)Linear mixed models with random intercepts for schools will be used for numeric data, such as anthropometric measurements, physical fitness, cognitive performance, and psychosocial health scores and haemoglobin concentration measurements.These models will include sex and age of the child, socioeconomic status of the parents or health status or fitness at the baseline survey as well as variables which were not perfectly randomised and might therefore act as confounders. Moreover, as intervention effects might depend on baseline characteristics of the child, stratified analyses and analyses involving interaction terms will be performed. The potential effect modifiers tested include sex, age, socioeconomic status of the parents or health status or fitness at the baseline survey.

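### The four intervention schools were purposively selected, yet the Data analysis section speaks of imperfect randomisation; the planned adjustment cannot be relied on to remove school-level confounding

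*Protocol article*

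**What the plan says.** The Study design section of the protocol article (text after the Fig. 3 caption) says the package will be "implemented in half of the schools, while the remaining schools will serve as controls". With eight schools, that is four against four. It then explains the choice: "The intervention schools were either selected due to the soil-transmitted helminth prevalence, number of Grade 4 learners", followed by "geographical location and affiliation to a particular ethnic group or commitment of teachers or school staff". The selection is reported in the past tense. The article mentions no random draw of schools.

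The Data analysis section lists among its primary objectives "the effects of interventions on disease status and other health parameters". For binary outcomes, "Mixed logistic regression models with random intercepts for schools will be used to compare binary data"; linear mixed models with the same random intercept serve numeric outcomes. On covariates it says "These models will include sex and age of the child, socioeconomic status of the parents or health status or fitness at the baseline survey", and adds "variables which were not perfectly randomised and might therefore act as confounders".

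**The concern.** The two sections describe different allocations. One reports selection on stated criteria; the other presumes a randomisation that fell somewhat short. Only the first is backed by a description of what was done.

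The criteria are not neutral. Helminth prevalence is itself a study outcome. Location and ethnic affiliation plausibly track living conditions. "commitment of teachers or school staff" plausibly bears on grades, fitness and psychosocial scores, and on how well a school-delivered package is carried out. If the schools chosen differ from the others in these respects, an ineffective package could appear helpful or harmful. A reader who relies on the Data analysis wording would also give the result more causal weight than the design can bear.

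**Working it through.** **1. Allocation text side by side.** Study design: schools selected on helminth prevalence, Grade 4 numbers, location and ethnic affiliation, or staff commitment. Data analysis: some variables imperfectly randomised. The Abstract and the sections on school selection, sample size and ethics describe no random allocation either. The randomisation wording therefore has nothing to refer to.

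**2. What the planned model covers.**
- Named covariates: sex, age, parental socioeconomic status, baseline health status or fitness. All are at child or parent level.
- The 'or' before baseline status does not commit every model to the child's own baseline value of the outcome being analysed.
- School-level selection factors are reached only through the general clause on possible confounders; none is named.
- The random school intercept widens the standard error for clustering. It assumes that school effects are unrelated to arm, which purposive selection can violate.

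**3. The plan's own figure.** The Sample size section gives p = 0.03, B = 150, ICC = 0.15, SE = 0.025. Design effect = 1 + 149 × 0.15 = 23.35; n = 0.03 × 0.97 / 0.025² × 23.35 = 1087.2, rounded up to 1088. It reproduces, but concerns the precision of a prevalence, not the intervention comparison.

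**4. Information in four against four.** With 600 children per arm (4 × 150), the effective number per arm is 600 / 23.35 = 25.7. The standard error of a difference in means is √(2 × 23.35 / 600) = 0.28 SD. At school level, 8 − 2 = 6 degrees of freedom remain after intercept and arm. Each school-level factor costs one: 5 remain with one factor, 2 with four, 1 with five.

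**5. Worst-case illustrations (assumptions, not document figures).**
- *Numeric outcome, the four schools with the highest baseline means chosen, normal school effects.* Simulated difference between arms before any intervention: about 0.55 SD at ICC 0.15 and 0.30 SD at an assumed ICC of 0.05. Random allocation gives 0 on average.
- *Selection on commitment.* Bias in level = ρ × 1.45 × √ICC, where ρ is the assumed correlation of commitment with the school mean. With an assumed ICC of 0.10, ρ = 0.3 gives 0.14 SD and ρ = 0.7 gives 0.32 SD, before any baseline adjustment.
- *Helminth prevalence, the four highest schools chosen* (p = 3 %, ICC 0.15, 125 children per school from about 1000 / 8; the Sample size section itself uses 150). Expected observed baseline is 5.9 % against 0.1 %. If deworming halves prevalence in both arms and the package does nothing, the absolute difference in change is about 3.0 points: 0.5 × 5.8 = 2.9 from the common halving, and about 0.1 from regression to the mean.

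**6. The same helminth case on the planned logistic scale.** Odds ratio within the high arm: (0.0295 / 0.9705) / (0.059 / 0.941) = 0.485. Within the low arm: (0.0005 / 0.9995) / (0.001 / 0.999) = 0.500. Ratio of the two: 0.97. For common falls of 30 % and 80 % it is 0.98 and 0.95. The 3-point artefact almost vanishes for change in log-odds. That cancellation needs the baseline to be taken into account; a comparison of follow-up status alone would carry the starting difference forward.

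**The case against.** The article calls itself a longitudinal cohort study, lists its selection criteria openly and acknowledges confounders. It already plans some baseline adjustment and logistic models. The criteria stand under an either/or with no direction given: nothing says the schools with most infection or the keenest staff received the package, and size, location and ethnic affiliation could have been used to balance the arms. All of this stands, and it limits what can be said about size.

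Three stronger readings are tempting and should not be adopted.
- *The effect is confounded by a known amount.* The figures in step 5 assume extreme selection and partly assumed inputs. The 3-point difference in change does not apply to the planned logistic model.
- *Adjustment is impossible because five school-level factors leave one degree of freedom.* The plan proposes no such model, and the Study area section shows that location and ethnic group largely coincide.
- *The trial will be reported as near-randomised.* That rests on one phrase.

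The objection does not remove the contradiction, nor does it show how selection on staff commitment would be handled. Baseline adjustment helps with differences in starting level, but not with a school characteristic that affects change over time or delivery of the package.

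**Conclusion.** The point holds in a limited form. It is firm that the document reports purposive selection of four of eight schools, describes no randomisation, and yet words its analysis of a primary objective as if there had been one. It is also firm that child- and parent-level covariates with an optional baseline term, plus a random school intercept, cannot be relied on to remove confounding by how schools were chosen, above all by staff commitment.

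The size and direction of any bias are unknown. The most the arithmetic shows is that extreme selection could produce a difference before intervention (0.55 SD at ICC 0.15) about twice the 0.28 SD standard error of the comparison. The accurate statement is that the effect is open to confounding, not that it is shown to be confounded.

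**What to change.** The Discussion reports the baseline survey as done and the interventions as designed, and the schools are already selected, so randomising them is no longer a practical remedy. The changes are:

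1. Describe the intervention comparison as a non-randomised controlled comparison, delete the phrase about imperfect randomisation, and state which criterion selected each school.
2. Make adjustment for each child's own baseline value of the outcome mandatory in every intervention-effect model, replacing the present 'or'. Add at most one school-level factor, area or ethnic group; as a two-level factor it leaves 5 school-level degrees of freedom.
3. Add a leave-one-school-out sensitivity analysis (eight refits per outcome), to show whether any one school drives the result.
4. Word the conclusions on intervention effects as associations, and name residual confounding by school selection as a limitation.

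The cost is a weaker causal claim, slightly wider intervals and minor extra analysis. No new data are needed beyond a record of why each school was chosen.

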### Sample size

The sample size calculation for the study was based on achieving sufficient precision in estimating the prevalence of soil-transmitted helminth infections. We conducted our calculation under the following assumptions for the cross-sectional baseline study:i)a prevalence of soil-transmitted helminth infections, *p*, of approximately 3 %;ii)an average number of children per school, *B*, of 150; andiii)an intra-class correlation coefficient for the clustering of outcomes within schools, *ICC*, of 0.15.

Requiring the standard error of the respective prevalence, *SE*, not exceeding 2.5 %, we obtained a necessary sample size *n* of 1088 children, using the formula [23]$$ n\kern0.5em \cdot \ge \frac{p\cdot \left(1-p\right)}{S{E}^2}\left(1+\left(B-1\right)\cdot ICC\right) $$

As a consequence, eight clusters (schools) will be needed considering the fact, that with a total of 1200 children from eight schools, we can accommodate 10 % loss to follow-up.

### Study participants

Children will be invited to participate if they meet the following inclusion criteria: (i) are willing to participate in the study; (ii) have a written informed consent by a parent/guardian; (iii) are not participating in other clinical trials during the study period; and (iv) do not suffer from medical conditions, which will prevent participation in the study, as determined by qualified medical personnel. Approximately 1000 Grade 4 primary schoolchildren, aged around 8 to 12 years, from 8 schools will be recruited during the baseline survey.

